## Methods

### Study design

We use a pilot, randomized, sham-controlled, double-blind clinical study design. Twenty patients are being randomly assigned to PMC tDCS plus CIMT or sham tDCS plus CIMT groups. All outcomes are collected at pretest and at post-test after 5 weeks of intervention. At 3-month follow up, outcomes of hand function are collected to examine retention.

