#### Functional neuroimaging

Mechanisms of response: functional neuroimaging is the most important assay to measure changes in the brain occurring in recovery in stroke. By measuring changes in perfusion or blood oxygenation during movement of the paretic hand, one can infer the association of activity of a region with its role in dexterity. Functional neuroimaging, such as functional MRI (fMRI), has demonstrated that damage due to stroke downregulates activity in stroke-affected versus intact hemispheres. As recovery occurs, the balance in activity (as seen using fMRI) between bilateral hemispheres, returns
[37,41]. We are exploring whether delivering tDCS to PMC in the stroke-affected hemisphere helps restore this balance. Another form of functional neuroimaging, called resting-state fMRI
[57], is critical in identifying how, over the course of stroke recovery, functional connectivity (fc) evolves between widespread networks
[58]. We investigate whether fc is strengthened, particularly between PMC and M1, with application of tDCS in CIMT.

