#### Neurophysiology

Substrates of response: transcranial magnetic stimulation (TMS) noninvasively measures cortical and corticospinal neurophysiology
[59]. In the present pilot trial, TMS defines efficiency of conduction via residual corticospinal tracts
[56], the structural integrity of which is outlined with diffusion tensor imaging. TMS also measures conduction between both hemispheres relayed via transcallosal pathways; this conduction is normally inhibitory, that is, one hemisphere exerts inhibition upon another, and that in return exerts counter-inhibition. In stroke, balance of such inhibition is disrupted. Whereas inhibition from the intact stroke-affected hemisphere is exaggerated, that in the opposite direction is diminished
[60]. We explore whether tDCS delivered to PMC in the stroke-affected hemisphere improves the efficiency of corticospinal conduction and helps rebalance inhibition exerted between the intact and stroke-affected hemispheres.

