### Randomization

We are using randomization blocks in sizes of four, where two patients in a block are assigned to PMC tDCS plus CIMT and the other two to the sham tDCS plus CIMT group. Such block randomization prevents the possibility that several patients in a row would get randomized to tDCS or sham tDCS groups in the early part of the study. The order of patients in blocks is random, generated using an online tool. Allocations are concealed in an opaque envelope and hidden in a locked cabinet with restricted access; they are opened by an investigator not involved in data collection or analysis before the first day of treatment.

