### Sample size estimation

The sample size has been estimated based on previous studies that have paired invasive or noninvasive stimulation with rehabilitation
[8,9,12,17,31]. Because UEFM has been most commonly investigated across the majority of studies, we used the effect sizes calculated across these studies to generate several permutations of sample size and the corresponding extent of change in the UEFM score (Figure 
2) to estimate power. Using a method of simulations
[63] where 500 simulations were performed, we estimated sample sizes that would generate significant differences upon the UEFM based on a mixed-effects model. From this method, we have found that a sample size of 10 per group would yield 83% power (95% CI 79.41 to 86.19%) to detect differences between groups (PMC tDCS plus CIMT sham tDCS plus CIMT group), 99.6% power to note differences across time (95% CI 98.56 to 99.95%) and 97% power (95% CI 95.35 to 99.46%) to observe a group X time interaction (Figure 
2).

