To assess neural substrates of recovery, both groups will be compared for change in inter-hemispheric balance (fMRI), fc and transcallosal inhibition and corticospinal conduction (TMS) from pretest to post-test. To understand whether effects of interventions vary across patients and factors explaining such variance, an ideal method would have involved identifying clinical, pathologic and neural factors that would predict the change in UEFM. However, since the statistical power of the study may be inadequate to pursue this analysis, we will follow an alternative method. Patients who achieve ≥3.5 gain in the UEFM score (criterion of clinical improvement defined in a previous clinical trial of invasive cortical stimulation)
[8] after 5 weeks of the intervention would be called responders. We will investigate whether the proportion of responders versus nonresponders includes a greater majority of patients from the tDCS group (Chi-square analysis). More importantly, we will compare clinical, pathologic and neural indicators between responders and nonresponders (independent samples *t*-test). These will include: baseline UEFM, location of disease (Oxford Stroke classification: total anterior circulation or partial anterior circulation or lacunar strokes)
[66], residual function and integrity of corticospinal tracts on the stroke-affected side measured with TMS and diffusion tensor imaging respectively.

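### Neural markers are compared between arms on pretest-to-post-test change with no stated adjustment for the pretest value; ANCOVA would guard against chance imbalance and usually add precision at the cost of one degree of freedom

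*Protocol article*

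**What the plan says.** The analysis of neural substrates is one sentence in Statistical and data analyses: "both groups will be compared for change in inter-hemispheric balance (fMRI), fc and transcallosal inhibition and corticospinal conduction (TMS) from pretest to post-test". It names change as the quantity compared, and names no test, model or covariate. The general linear mixed model described just before it is tied to the functional outcomes.

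The hypotheses behind the comparison are about an abnormal balance moving back towards normal. Under Functional neuroimaging: "We are exploring whether delivering tDCS to PMC in the stroke-affected hemisphere helps restore this balance". Under Neurophysiology, the question is whether premotor stimulation "helps rebalance inhibition exerted between the intact and stroke-affected hemispheres".

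On size and allocation, Study design says "Twenty patients are being randomly assigned to PMC tDCS plus CIMT or sham tDCS plus CIMT groups", and Randomization says "We are using randomization blocks in sizes of four", half of each block to each arm. No stratification factor is described. Markers of neural recovery places the imaging and neurophysiology at both pretest and post-test, so a pretest value of each marker is available for both arms.

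**The concern.** A difference in change uses the pretest value only by subtraction, which amounts to fixing its regression coefficient at 1. Where a marker is imperfectly repeatable the true coefficient is smaller, so subtraction over-corrects for any pretest difference between the arms. An arm that happens to start further from balance will tend to move back towards it without any stimulation effect. That is the same direction as the hypothesised effect.

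The sponsor will interpret a single randomisation of 20 patients. If the stimulated arm happens to start less balanced, the estimate leans towards apparent rebalancing. If it starts better balanced, a real effect is partly hidden. Separately, a comparison this small has little precision to spare, and the information that would recover some of it is already being collected.

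**Working it through.** **Plan's own figure.** None is given for the neural markers. The printed power figures are for the upper extremity Fugl-Meyer score: "a sample size of 10 per group would yield 83% power (95% CI 79.41 to 86.19%) to detect differences between groups" and "97% power (95% CI 95.35 to 99.46%) to observe a group X time interaction". They cannot be rebuilt, because the text gives no effect size, SD or correlation. The exact binomial interval for 415 of 500 simulations is 79.41 to 86.19%, as printed. For 486 of 500 (97.2%) it is 95.35 to 98.46%, so the printed upper limit of 99.46% does not reproduce. That is a separate matter and has no bearing here.

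**Inputs.**
- n = 10 per arm: 20 patients in blocks of four is 5 blocks, 2 per arm in each (Study design, Randomization; also Sample size estimation).
- Marker SD set to 1 and taken as equal at pretest and post-test (assumption).
- rho: not in the article; assumed 0.3 to 0.9.
- Two-sided 5% test. Sidedness is not stated (assumption).
- True effect of 1 SD for the power illustration (assumption).

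**Step 1: overall validity.** In 40,000 simulated null trials per rho, the change contrast averaged 0 and rejected in 4.9 to 5.1% at every rho. There is no unconditional bias and no inflation of type I error.

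**Step 2: how often the arms start apart.** The SD of the pretest difference is √(2/10) = 0.447. So P(|difference| > 0.5 SD) = 2 × [1 − Φ(0.5/0.447)] = 0.264 per marker. Over the four markers named, the expected number with a gap this large is 4 × 0.264 = 1.06, whether or not the markers are correlated.

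**Step 3: what a gap does.** With no treatment effect and a pretest difference d, the expected change contrast is −(1 − rho) × d. Simulation of 200,000 null trials per rho, restricted to those with a gap above 0.5 SD, gave:

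| rho | mean shift (SD) | change test rejects |
|---|---|---|
| 0.3 | 0.51 | 11.4% |
| 0.5 | 0.36 | 9.7% |
| 0.7 | 0.22 | 7.5% |
| 0.8 | 0.14 | 7.0% |
| 0.9 | 0.07 | 6.0% |

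At rho 0.3 to 0.7, at least 96% of these rejections favour the arm that started lower. In the same trials ANCOVA had mean error near 0 and rejected in 4.9 to 5.1%.

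**Step 4: precision.** The variance of the arm difference is 2(1 − rho) × 0.2 for change. For ANCOVA it is (1 − rho²) × 0.2 × (1 + 1/16), the last factor being the average cost of estimating the slope. At rho 0.5 these are 0.200 and 0.159, a ratio of 0.80. Power is for a true effect of 1 SD.

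| rho | variance ratio, ANCOVA/change | power, change | power, ANCOVA |
|---|---|---|---|
| 0.3 | 0.69 | 43% | 57% |
| 0.5 | 0.80 | 56% | 66% |
| 0.7 | 0.90 | 78% | 82% |
| 0.8 | 0.96 | 92% | 93% |
| 0.9 | 1.01 | 99.7% | 99.6% |

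**The case against.** A reader might infer that regression to the mean makes this test produce a false mechanism. The documents do not support that. The planned comparison is between randomised arms, and regression to the mean acts on both equally in expectation, as step 1 confirms. It would pass for recovery in a within-arm before-and-after reading, which the quoted sentence does not plan. The raised rejection rates in step 3 belong only to the 26% of trials with a large gap. At rho 0.3 the remaining trials must reject in about (5.0 − 0.264 × 11.4)/0.736 = 2.7%. A false positive for stimulation in a trial where that arm started more than 0.5 SD lower occurs in at most 0.132 × 11.4% = 1.5% of all trials, within the nominal 2.5% for that direction.

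A reader might also infer that the article commits itself to ignoring the pretest value. It does not: subtraction uses that value, no model is named, and covariates are often left to a fuller plan. The abstract speaks of a mixed model analysing changes, so the word change need not mean a t-test on differences. This stands, and it limits the point. It does not remove it, because change is the only quantity the text fixes for these markers. Reading it as a group-by-time term would not help by itself: with two time points and complete data, an unconstrained repeated-measures model gives the same contrast as the change score.

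Finally, the markers are exploratory, no power is claimed for them, and the gain depends on a correlation the article does not give. All of that stands.

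**Conclusion.** The point holds as one of efficiency and of protection against chance imbalance. The stated comparison is valid on average, but it is exposed to a pretest gap that is common at 10 per arm, and it is less precise than it need be unless the markers are highly repeatable. If rho is about 0.7 or below, the variance reduction is some 10 to 31%, and a gap above 0.5 SD moves the estimate by 0.22 to 0.51 SD on average. If rho is 0.8 to 0.9, the precision gain is negligible or nil and the shift is 0.07 to 0.14 SD. These sizes rest on the assumed rho, on equal SDs at the two visits and, for power, on an assumed effect of 1 SD. Nothing here invalidates the test or any other analysis in the article.

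**What to change.** In the sentence on neural substrates in Statistical and data analyses, replace the comparison of change with an ANCOVA for each marker: post-test value as outcome, arm as factor, and that marker's own pretest value as covariate. Report the adjusted arm difference with its 95% CI, and describe raw change only as supplementary. If adjustment was already intended, a clause saying so is enough.

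The cost is one sentence and one residual degree of freedom (17 in place of 18). No new data or visits are needed. At rho 0.9 the change score is as precise or marginally better (variance ratio 1.01), so little is lost even where the adjustment brings no gain in precision.

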[69]. If we find that responsive patients show distinctive characteristics, such as patent and functioning white matter tracts et cetera, then these would serve as entry criteria for the future. Unfortunately it may also mean that stimulation may be more fruitful only for a limited few, but this information would optimize resource allocation. For patients showing limited to no response, we would identify whether functioning of alternate areas (as identified on fMRI) and patency of tracts from other regions (from tractography) may hold greater meaning. A patient-guided approach to utilizing such residual resources will then be created, employing alternate rehabilitation methods and/or stimulating patient-specific loci.

Knowing mechanisms of long-term pairing can help address why chronic effects are not as robust. Even though singular sessions or short-term paradigms show benefit
[11,13,16,22,29,30], trials incorporating long-term training have failed to witness an advantage
[15-19]. Divergent success across short- and long-term studies may also be an effect of dosage. Stimulation may have an initial accelerative effect
[25,32] manifested in the short term, but over the long term, the effect of rehabilitation itself may become robust
[37,70], diminishing the comparative effect size.
[15-19]. Confounding from individual variance may also factor in; if stimulation in rehabilitation were truly effective, its differences from rehabilitation would evolve over time; on the flip side, if all gains were solely related to variance across individuals, then a long-term study would show no difference, and short-term studies would be easily confounded. Short-term designs also have the added advantage of higher treatment fidelity; standardized laboratory-based paradigms can be delivered in short-term approaches more easily
[13,14,22,29,45], whereas longer protocols of clinical rehabilitation suffer from variance in treatment delivery
[8-10,16,17,23-25,30,44]. However, exploring stimulation delivered with long-duration rehabilitation still carries greater clinical utility, despite challenges to adherence and fidelity, because short-term paradigms, though invariably positive, do not correlate with long-term outcomes
[13,14,22,23,29-31,45].

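### The responder analysis cannot show whether the tDCS effect varies across patients: one test measures the average effect, the other, as written, measures prognosis pooled over arms

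*Protocol article*

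**What the plan says.** In the protocol article, Statistical and data analyses (efficacy and markers of recovery), the aim is given as "To understand whether effects of interventions vary across patients and factors explaining such variance". The authors would have preferred to identify factors that predict change in UEFM, but "since the statistical power of the study may be inadequate to pursue this analysis, we will follow an alternative method".

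The substitute has three steps.

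- **Label.** "Patients who achieve ≥3.5 gain in the UEFM score" "after 5 weeks of the intervention would be called responders". The cut-off is taken from an earlier trial of invasive stimulation, where it marked clinical improvement. It is applied to patients in both arms.
- **First test.** "We will investigate whether the proportion of responders versus nonresponders includes a greater majority of patients from the tDCS group (Chi-square analysis").
- **Second test.** "we will compare clinical, pathologic and neural indicators between responders and nonresponders (independent samples" *t*-test). The indicators are baseline UEFM, stroke location, and corticospinal function and integrity. No arm term, within-arm comparison or arm-by-marker term is stated.

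The Discussion says what would follow. If responders turn out to have distinctive characteristics, these become entry criteria for later trials, and "Unfortunately it may also mean that stimulation may be more fruitful only for a limited few". It continues: "For patients showing limited to no response, we would identify whether functioning of alternate areas" and tracts from other regions matter more, leading to other rehabilitation methods or stimulation sites. Objective 2 (Objectives and hypotheses) is likewise comparative: markers of response to the paired treatment as against CIMT alone.

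**The concern.** The aim concerns variation in an effect, but the label records a change. Under Study design each patient is assigned to one arm and is measured once before and once after the intervention, so no patient's own tDCS effect is observed. Under CIMT all patients receive the same rehabilitation. A gain of 3.5 points therefore combines the CIMT effect, practice, rating error and, in one arm only, whatever tDCS adds. A sham patient can be a responder.

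Neither planned test repairs this. Comparing responder shares by arm shows whether tDCS raises the average chance of a gain. Comparing markers between all responders and all nonresponders shows which patients do well, whatever they received. A marker can predict gain strongly while the tDCS effect is the same in everyone, or absent.

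What is at stake is the choice of patients for later stimulation trials, which the article presents as a main product of the pilot. A purely prognostic marker could become an entry criterion for stimulation.

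**Working it through.** **Inputs from the article:** 10 patients per arm (Sample size estimation), cut-off 3.5 points, significance level 0.05 (Figure 2 legend; taken as two-sided). The article states power for group, time and their interaction, but no figure for the responder analysis, so there is none to reproduce.

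**Assumptions (not in the article):** normally distributed gains, SD of change 4 points, and the mean gains and marker correlations shown below. Simulated rates rest on 4,000 runs per scenario.

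**1. The chi-square by arm follows the average effect.**
- Identical effect of 3.5 points in every patient, sham mean gain 2. P(gain ≥ 3.5) is P(Z ≥ 1.5/4) = 0.35 in the sham arm. In the tDCS arm the mean is 5.5 and the probability is P(Z ≥ −2/4) = 0.69. Simulated rejection rate: 31%, with no variation in effect.
- Strong variation, zero average effect. The mean gain is 3.5 in both arms, and the tDCS effect changes by 4 points per SD of a marker. The tDCS-arm SD is √(4² + 4²) = 5.66 against 4 in the sham arm, but P(gain ≥ 3.5) is 0.50 in both. Simulated rejection rate: 4%.

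**2. The pooled *t*-test follows prognosis.** Suppose there is no tDCS effect, the mean gain is 3.5 and a marker has correlation *r* with gain. The cut-off then splits at the mean, and the SD of change drops out.
- Difference in mean marker, in marker SDs: 2*r*√(2/π) = 1.596*r*, which is 0.80 for *r* = 0.5 and 1.12 for *r* = 0.7.
- Within-group SD: √(1 − 2*r*²/π) = 0.917 and 0.829.
- Standardised difference: 0.87 and 1.35.
- With about 10 patients in each label group, multiply by √5: 1.95 and 3.01. The critical value on 18 df is 2.10.
- Approximate rejection rate: Φ(1.95 − 2.10) = 44% and Φ(3.01 − 2.10) = 82%.
- Simulation gives 43% and 79%, which agrees.

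With an identical 3.5-point tDCS effect in everyone (sham mean 2), the simulated rates are 34% and 68%.

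**3. An arm-by-marker interaction addresses the stated question.** In all the scenarios without variation in effect, its rejection rate is 4% to 6%. When the effect does vary by 4 points per marker SD, it rejects in about 46%, against 17% to 22% for the pooled *t*-test.

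**4. The spread of gains also bears on it, with low precision.** If tDCS added the same amount to everyone, the SD of change would be the same in both arms. With 9 and 9 degrees of freedom the 95% CI for the SD ratio runs from 0.498 to 2.006 times the observed ratio (square roots of the F(9,9) quantiles). The chance that it excludes 1 is about 16% at a true ratio of 1.41 (5.66/4 above), 20% at 1.5 and 50% at 2.0.

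**The case against.** Four points can be made for the authors.

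- **The plan does not infer variation merely because both labels occur.** This stands. A reader might infer that it does, since a split is very likely under a constant effect: 97.5% to 99.8% among 10 tDCS patients with mean gain 2 to 5 and SD 3 to 5. The document does not support that reading. The labels feed two tests, and the Discussion's inference is conditional on responders having distinctive characteristics. The split probability also depends on assumed values and falls to 14% at mean 10, SD 3. The defect lies in what the two tests measure.
- **This is an exploratory pilot, and the authors call the method second best.** This stands as to weight. But what they concede is low power, not that the substitute answers a different question. Their preferred analysis, predicting change in UEFM, would also be prognostic unless it contained arm-by-marker terms.
- **The wording is cautious and concerns future studies.** True: no trial patient's treatment depends on the label. Caution about strength does not help if the comparison cannot separate prognosis from variation in effect.
- **The alternatives are weak at this size.** Also true. In addition, equal spread would not prove a uniform effect: a tDCS effect negatively related to CIMT gain, or the 66-point ceiling of the UEFM, could hide variation. Weak evidence on the right question, reported with its interval, is still preferable to a test of another question.

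**Conclusion.** The concern holds in this form: neither planned test can show whether the tDCS effect varies across patients, and the Discussion's step from responder characteristics to entry criteria for stimulation does not follow from them.

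The size depends on quantities the article does not give. With no tDCS effect and a mean gain near 3.5, a prognostic marker is significant in about 43% of trials if it correlates 0.5 with gain and about 80% if it correlates 0.7. A marker unrelated to gain stays near 5%. The logical point needs none of these values: it rests on all patients receiving CIMT, each being in one arm, and the stated comparison pooling the arms.

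A reader might also infer that the spread of gains is the only randomised evidence on variation. It is not, because the indicators are to be measured in all patients and the interaction can be estimated.

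This leaves the primary UEFM analysis untouched. It should be corrected before analysis because the marker results are meant to shape patient selection in later trials.

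**What to change.** **In Statistical and data analyses:**
- Call the two groups *improved / not improved*, which matches the source of the cut-off, and describe the pooled marker comparison as prognostic.
- As exploratory evidence on variation in the tDCS effect, report (a) the tDCS-to-sham ratio of the SD of 5-week UEFM change with its 95% CI and (b) the arm-by-marker interaction estimates with 95% CIs. Name the markers in advance and report all of them. With five independent intervals, for example, the chance that at least one excludes no difference by accident is 1 − 0.95⁵ = 23%.

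**In the Discussion:**
- Allow the statement that stimulation helps only some patients only if such an interval excludes no difference (ratio 1, or interaction 0). A larger observed spread in the tDCS arm is not enough, since that happens half the time when the true spreads are equal.
- Otherwise state that variation in the tDCS effect was not shown. Do not present equal spread as proof of a uniform effect.

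**Cost:** a few extra estimates from data already being collected, plus wording. The drawback is imprecision. An observed SD ratio of 1 would carry an interval of about 0.50 to 2.0, so the likely result is *not shown*.

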**Figure 2 F2:**
[figure not shown]
**Power analysis: power was determined by simulation.** Lower and upper lines define exactly the 95% CI for power, calculated based on the binomial distribution. N is the total sample size. The analysis was performed at a 0.05 significance level considering 2 × 2 factorial analysis of variance (ANOVA) (tDCS plus CIMT and sham tDCS plus CIMT from pretest to post-test). Power has been estimated here for an interaction term (A *C).

Although the estimated sample size appears small, it is commensurate with the pilot exploratory nature of our study. Pilot studies involving brain stimulation generally use smaller sample sizes compared to rehabilitation trials
[28] because contraindications to brain stimulation/imaging are constraining. Still, we anticipate having adequate statistical power based on prior evidence where despite enrolling a total of 14 to 30 subjects, several studies report significant benefit of adjunctive stimulation
[8,30,44]. Additionally, use of a repeated-measures design further provides greater power. Studying neural mechanisms with fMRI and tractography in limited sample sizes is challenging. Given the exploratory nature of our pilot study, we would be able to highlight elemental neural mechanisms of recovery. Previously, in a three-group, randomized controlled study design with a small sample of 20, we deciphered correlates of fMRI
[37]. Recently too, Stagg *et al*.
[64] show differences in fMRI activation across varying types of tDCS interventions in 11 patients with stroke. Without overemphasizing the importance of small pilot studies, we stress instead the significance of large-scale studies in generating clear evidence of efficacy. Our current pilot exploratory study is a step in that direction as it would offer estimates of effect size related to PMC tDCS and neural markers that can serve as entry criteria.

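### Low power may excuse dropping a joint prediction model, but not replacing continuous UEFM change with a ≥3.5-point responder split, which lowers power further for each marker

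*Protocol article*

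**What the plan says.** The Study design section gives the sample: "Twenty patients are being randomly assigned to PMC tDCS plus CIMT or sham tDCS plus CIMT groups". The part of Statistical and data analyses on efficacy and markers of recovery then asks whether intervention effects vary between patients and what explains the variation. It names its preferred approach: "an ideal method would have involved identifying clinical, pathologic and neural factors that would predict the change in UEFM". It drops that approach on one ground: "since the statistical power of the study may be inadequate to pursue this analysis, we will follow an alternative method".

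The alternative begins with a cut-point: "Patients who achieve ≥3.5 gain in the UEFM score" after 5 weeks are called responders, a criterion taken from an earlier trial of invasive cortical stimulation. Indicators are then compared between responders and nonresponders by independent-samples t-test. Those listed are baseline UEFM, lesion location (an Oxford classification with three categories), and the function and integrity of the corticospinal tracts. No power is given for either the dropped analysis or its replacement. The Sample size estimation section and the Discussion say that markers found this way could become entry criteria for later trials.

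**The concern.** The replacement uses the same patients and the same change score, but keeps only whether each gain reached 3.5 points. A gain of 4 and a gain of 12 count alike, while 3 and 4 are treated as different in kind. Dichotomising an outcome loses information, so if power is the worry, this step adds to it.

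Two separate decisions sit under one justification. The first is to test indicators one at a time rather than jointly, which does help in a small sample. The second is to replace continuous change by a two-class outcome, which does not. The text does not consider the option that takes the first without the second. At stake is a higher chance of missing a real marker, and less precise estimates passed on to the design of later trials.

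**Working it through.** **Inputs from the protocol article.** n = 20 (Study design). Allocation is 1:1 in blocks of four (Randomization): "two patients in a block are assigned to PMC tDCS plus CIMT and the other two to the sham tDCS plus CIMT group"; hence 10 per group. Alpha is 0.05 (Figure 2 legend: "The analysis was performed at a 0.05 significance level"); sidedness is not stated and two-sided is assumed. The cut is a UEFM gain of at least 3.5.

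**Assumed, because the article does not give them.** Marker–gain correlation ρ from 0.3 to 0.7, responder share q from 20% to 70%, and bivariate normal marker and gain.

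**The plan's own figure.** The only stated powers concern the UEFM mixed model, for example 83% (95% CI 79.41 to 86.19%) for the group difference, from a calculation "where 500 simulations were performed". The text gives no effect size or SD, so the 83% cannot be recomputed. Its interval can be checked: the exact binomial interval for 415/500 is 79.41 to 86.19%, which agrees. None of this bears on the marker analysis.

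**Information kept by the split.** Cutting a normal gain at c, so that a share q lies above it, multiplies the correlation by f = φ(c)/√(q(1−q)). The information kept is f².

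- q = 50%: f = 0.399/0.500 = 0.80; f² = 0.64; 20 × 0.64 ≈ 13 effective patients.
- q = 30%: f = 0.348/0.458 = 0.76; f² = 0.58; 20 × 0.58 ≈ 12.
- q = 20%: f = 0.280/0.400 = 0.70; f² = 0.49; 20 × 0.49 ≈ 10.

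**Power by simulation** (20,000 replicates per cell). The continuous analysis tests t = r√(n−2)/√(1−r²) on 18 df. The alternative is the pooled t-test of the marker between responders and nonresponders.

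| ρ | Continuous change | Split, 50% responders | Split, 30% | Split, 20% |
|---|---|---|---|---|
| 0.3 | 25% | 17% | 16% | 14% |
| 0.4 | 43–44% | 29% | 25% | 22% |
| 0.5 | 64–65% | 44% | 38% | 33% |
| 0.6 | 84% | 61% | 55% | 46% |
| 0.7 | 96% | 80% | 73% | 62% |

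Repeat runs at ρ = 0.5 moved these figures by about one point (43–44%, 38–39%, 32–33%). With ρ = 0, both tests reject about 5% of the time. Across all non-null cells the split loses about 8 to 38 points. About 80% power needs ρ near 0.58 with continuous change, but near 0.70 with the split even at 50% responders.

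**Adjusting for group.** Adding randomised group to the continuous model at ρ = 0.5 leaves about 61%.

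**Other distributions, ρ = 0.5.** With whole-number gains (assumed SD 4), power is 63–65% against 43%, 39% and 33% at 50%, 30% and 20% responders. With strongly right-skewed gains, Pearson gives 54% and Spearman 56–57%, against 43%, 40% and 32%.

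**Joint model, ρ = 0.5 for one true marker.** With 4 predictors, power is 40–56%; with 8, it is 27–42% (correlation between predictors 0 to 0.5). In the same runs the responder t-test gave about 42–44%, and the one-at-a-time test on continuous change about 64%.

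**The case against.** The strongest defence is that the dropped analysis was a joint model. Several classes of factor predicting one outcome reads naturally that way, and with many correlated predictors such a model can fall below the responder t-test. A reader might infer that the authors' reason is simply backwards. The article does not support that, because it never says whether the analysis it rejected was joint or one factor at a time. This part of the objection stands. What it does not do is defend the split: the advantage over a large joint model comes from testing one marker at a time, which continuous change allows equally.

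The 3.5-point cut also has an external clinical source and suits the aim of selecting patients for later trials. That is a good reason to report it, but it is not the reason the article gives for setting the continuous analysis aside.

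A reader might carry the 64% over to a model that also adjusts for baseline UEFM. That is not supported. At ρ = 0.5 such a model gave about 43% (marker–baseline correlation 0.5, baseline–gain 0.3) to about 75% (0.5 and 0), and it fell to 35% in a run with marker–baseline correlation 0.7. It asks a stricter question, namely the marker's value beyond baseline.

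Finally, a continuous main-effects analysis does not show whether the effect of stimulation differs by marker. The pooled responder comparison does not show this either, so the change repairs precision only.

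**Conclusion.** The concern holds in a limited form. Low power can justify leaving out a joint many-predictor model; it cannot justify dichotomising the change score. For one continuous marker with an assumed correlation of 0.5, the split costs about 20 to 32 points of power as the responder share falls from 50% to 20%. The size depends on the assumed correlation and responder share, but the direction was the same in every one-marker scenario tried. The figures do not apply to lesion location, which is categorical.

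The weight is moderate. A reader might take the marker analysis to be the main product of the pilot, but Objectives and hypotheses lists it second, after safety, feasibility and effectiveness, and the study is described as exploratory. For correlations of 0.3 to 0.4, continuous change gives only 25–44% and the split 14–29%, so the authors' worry about power is itself reasonable.

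**What to change.** 1. Analyse each indicator singly against continuous UEFM change, adjusted for randomised group, and report the estimate with its 95% CI. Use Spearman correlation as a check for continuous markers.
2. For lesion location, compare mean UEFM change across the categories.
3. Analyse baseline UEFM as a marker in its own right; it cannot be both the marker and a covariate in one model.
4. For the other markers, report a baseline-adjusted version as a sensitivity analysis, stating that it addresses value beyond baseline and that its power depends on correlations not yet known.
5. Keep the ≥3.5-point responder comparison as a descriptive display.
6. Reword the rationale: limited power is why no joint many-predictor model is fitted, and indicators are therefore examined one at a time.

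The cost is a change of wording and slightly more analysis work on data already being collected. It does not make the marker aim well powered.
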